#### Website user statistics

Website user statistics will be collected for each participant. These will be measured by google analytics software, and include number of website visits, average number of pages viewed during a visit, and average visit duration during the 8 week intervention period and during the 12 month post intervention period leading up to the follow up questionnaires.

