## Background

Physical activity improves physical and mental health, and significantly lowers the risk of non-communicable disease including cardiovascular disease, diabetes mellitus and cancer [1]. It is estimated that individuals who are physically active have a 30% to 50% lower risk of non- communicable diseases and have a 20% to 50% lower risk of mortality than inactive individuals [2-4]. The World Health Organisation recommends 30 minutes of moderate intensity activity on 5 days of the week to receive health benefits and reduce the risk of non-communicable disease [5]. Despite this, more than 50% of Australians fail to meet these recommendations [6] which is estimated to cost the Australian economy 13.8 billion each year in healthcare, loss of productivity, and mortality costs [7]. Hence, there is an urgent need for effective physical activity interventions with a broad reach.

High levels of internet access (e.g. 83% in Australians) make the development and dissemination of web-based physical activity interventions worthwhile [8]. Health behaviour change interventions delivered via the internet have the potential to reach a large audience at low-cost, they are convenient for participants and enable the content to be delivered in a non-confrontational way [9-11]. Although the short-term effectiveness of web-based physical activity interventions is well-established, participant retention and engagement have been identified as a challenge with many web-based interventions reporting high dropout rates or low use of the websites after a period of time [12,13]. As the amount of exposure to the intervention content is strongly linked to behavioural outcomes, low participant retention and engagement may limit the effectiveness of web-based interventions [14,15].

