### Procedure

Participants will be randomly assigned to one of three groups, tailoring + video-coaching, tailoring-only or wait-list control. All tailoring groups will receive a web-based physical activity intervention named ‘*My Activity Coach*’ that consists of 4 modules of computer-tailored advice. Additionally the tailoring + video-coaching participants will also receive 4 brief coaching sessions with a physical activity expert to discuss the personalised advice they received in the previous module. To control for exposure to additional intervention contacts in the tailoring + video-coaching groups the tailoring-only participants will receive a total of 4 tailored emails to remind them of the tailored advice they received in the previous module, but they will not receive any coaching. Questionnaire data will be collected at baseline, immediately post-intervention at week 9, and 6 and 12 months post baseline (see Figure 1). All questionnaires will be completed through the intervention website, including the waitlist control group (though no tailored content will be available for these participants). Satisfaction with the intervention will only be measured at 9 weeks in intervention group participants. Participant retention, engagement, and feasibility of the coaching sessions will be measured for the intervention participants throughout the intervention. Participants in the wait-list control group will be given the opportunity to participate in the intervention after they have completed the 12-month follow-up questionnaire (see Figure 1). The research has been approved by the Central Queensland University Human Ethics Committee (H13/04-044), and complies to the Helsinki Declaration.

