### Measures

Participants will receive a total of 4 questionnaires to assess their physical activity, the correlates of physical activity related to the Theory of Planned Behaviour and quality of life across 4 time points (baseline, immediately after the end of the intervention (week 9), at 6 months and at 12 months post-baseline). Participant’s demographics and satisfaction with the intervention will only be assessed in the baseline and post intervention (week 9) questionnaires respectively. The satisfaction questions will only be given to the intervention groups, as the wait-list control participants will not have completed the intervention at this time point (week 9). The individual measures included in the questionnaires are explained below. Participant engagement, participant retention, and video-coaching feasibility will be measured throughout the intervention. Video-coaching feasibility will be measured by participant satisfaction and fidelity of the video-coaching sessions, and intervention engagement will be measured through website user statistics and intervention fidelity which are explained in detail below.

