### Statistical analyses

#### Intervention effects

Data will be analysed using intention-to-treat principles. Physical activity will be modelled using the using linear mixed models with random intercepts, the fixed effects of group (control, tailoring only, tailoring + video-coaching) and time (baseline, post-intervention, 6-months, 12-months), and a group by time interaction and will adjust for potential confounders including gender, age, education, income, employment, location, marital status and BMI if they are associated with physical activity and time.

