#### Secondary analyses

The secondary analyses will be conducted using linear effects modelling to determine the effect of group and time on Theory of Planned Behaviour constructs and quality of life. Linear mixed modelling will also be used to compare retention, satisfaction, intervention fidelity and website user statistics between groups. Multiple regression analyses will be conducted to assess Theory of Planned Behaviour concepts including intention, attitude, subjective norm, perceived behavioural control and planning as mediators for physical activity changes. Multiple regression analyses will also be used to asses these Theory of Planned Behaviour concepts as well as demographic variables (age, gender, income, marital status, education and BMI) as moderators for physical activity changes. Descriptive statistics will be used to assess participant satisfaction and fidelity of the video-coaching session.

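### Two of the three website engagement statistics are per-visit averages, defined only for visitors, so their between-group comparison can miss or run against a difference in total exposure

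*Protocol article*

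**What the plan says.** All references are to the protocol article.

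- **Measures**: engagement has two parts: "intervention engagement will be measured through website user statistics and intervention fidelity which are explained in detail below".
- **Website user statistics**: the unit is the individual ("Website user statistics will be collected for each participant"). For the first window the article lists "number of website visits, average number of pages viewed during a visit, and average visit duration during the 8 week intervention period". The same statistics are then taken in a second window, described this way: "and during the 12 month post intervention period leading up to the follow up questionnaires". That is one count and two averages per visit, in two windows. Total pages and total time are not listed.
- **Secondary analyses**: "Linear mixed modelling will also be used to compare retention, satisfaction, intervention fidelity and website user statistics between groups".
- **Intervention fidelity**: completion of the module surveys and whether they were on time are also recorded. These are defined for people who never log in.
- **Background**: low website use over time is described as a known problem in this field, and the reason for caring about engagement is given: "As the amount of exposure to the intervention content is strongly linked to behavioural outcomes".

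**The concern.** Each average has the participant's own visit count as its denominator, which has two consequences.

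First, a participant with no visits in a window has no average. Unless some value is assigned, a mixed model on that statistic leaves the participant out for that window. What is then compared is visitors with visitors, a subset formed after randomisation and possibly differently in each arm. This is most likely to matter in the post-intervention window, when no new modules, alerts or reminders bring people back.

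Second, an average per visit is not a measure of how much of the programme a person used. It falls when a person adds visits shorter than their current mean.

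The trial asks whether coaching improves engagement. If coaching keeps marginal users coming back for short visits, two of the three website results could show no benefit, or an apparent disadvantage, while total use is higher.

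**Working it through.** The article gives no engagement figure, so there is none to reproduce. The form of the statistic comes from Website user statistics. Every visit rate and visit length below is an assumption, because the article states none.

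**1. The statistic.** For a participant with V visits and total time (or pages) T, the average is A = T / V.
- V = 0 gives 0/0, so there is no value.
- One more visit of length d gives (T + d) / (V + 1), which is below T / V exactly when d < T / V. The total T rises in every case.

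**2. One person.** Four visits of 20 minutes and 10 pages: T = 80 minutes and 40 pages, averages 20.0 and 10.0. Add four visits of 3 minutes and 2 pages:
- time: total 80 + 12 = 92 minutes, average 92 / 8 = 11.5
- pages: total 40 + 8 = 48, average 48 / 8 = 6.0

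If the four added visits are also 20 minutes long, the average stays at 160 / 8 = 20.0.

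**3. Two arms.** In arm 1 a share p returns (core users), with v visits each of length c. Arm 2 has the same core users plus an extra share e, with v visits each of length m.
- Average among visitors: c versus (pc + em) / (p + e). Difference: e(m − c) / (p + e).
- Total per randomised participant, zeros included: vpc versus v(pc + em). Difference: vem, always positive.

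The sign of the first difference depends on m − c, that of the second does not. With v = 3:

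| Returning | c, m (min) | Average among visitors (min) | Total per randomised (min) | Visits per randomised | No value |
|---|---|---|---|---|---|
| 40% vs 70% | 12, 6 | 12.0 vs 9.4 | 14.4 vs 19.8 | 1.2 vs 2.1 | 60% vs 30% |
| 40% vs 70% | 10, 10 | 10.0 vs 10.0 | 12.0 vs 21.0 | 1.2 vs 2.1 | 60% vs 30% |
| 30% vs 50% | 12, 6 | 12.0 vs 9.6 | 10.8 vs 14.4 | 0.9 vs 1.5 | 70% vs 50% |

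First row: (0.4 × 12 + 0.3 × 6) / 0.7 = 6.6 / 0.7 = 9.4, which is 21% below 12.0. The totals are 3 × 0.4 × 12 = 14.4 and 3 × 6.6 = 19.8, the second about 37% higher.

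**4. Less non-use.** Core users average 20 minutes per visit, and users kept only in the coaching arm average 8.
- Non-use 5% (coaching) versus 25% (tailoring-only): among users (75 × 20 + 20 × 8) / 95 = 17.5 versus 20.0. With non-users counted as zero, 1660 / 100 = 16.6 versus 1500 / 100 = 15.0.
- Non-use 0% versus 10%: among users (90 × 20 + 10 × 8) / 100 = 18.8 versus 20.0. With zeros, 18.8 versus 18.0.

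The reversal therefore does not need heavy non-use, but it does need the extra users' visits to be shorter.

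**The case against.** Much of the opposing case stands.

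- **Direction.** A reader might infer that the more engaged arm will be ranked lower. The documents do not support that. They give no visit lengths, and step 3 shows that the average ties when m = c and favours the more engaged arm when m > c. The coaching arm alone books sessions through the site, which could create short visits. But booking is requested straight after a module and may fall in the same visit.
- **Dropping non-users.** A reader might infer that the plan discards non-users in breach of intention to treat. It does not say so. A rule for windows without visits may be in an analysis plan that is not shown. The sentence "Data will be analysed using intention-to-treat principles" stands under Intervention effects, directly before the physical activity model.
- **What engagement means.** The Background sentence on exposure is motivation. It does not define the outcome, and the statement in Measures does not require each component to rise with exposure.
- **Questionnaire visits.** It is true that "All questionnaires will be completed through the intervention website, including the waitlist control group", so such visits might seem to inflate average duration. The article does not say that they count. The first window is 8 weeks and the first follow-up questionnaire is at week 9, and the wording of the second window can be read as ending before the questionnaires.
- **Other measures.** Visit count and module completion are defined for everyone, and the list of website statistics is open-ended. During the 8 weeks, emails and a reminder call make zero visits less likely.

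One thing is not answered by this. No rule for zeros makes a per-visit average rise with total use, and the article itself names these averages among the statistics to be compared between groups.

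**Conclusion.** The point holds in a limited form. Average pages per visit and average visit duration are conditional on visiting and need not track total use. Comparing them between groups is a comparison among self-selected visitors, which can miss a difference in total exposure and under some visit patterns contradict it. On the assumed inputs the result ranges from a tie in the averages with totals of 12 versus 21 minutes, to a 21% lower average with a total about 37% higher. The mechanism is arithmetic. Its size and direction in this trial are unknown.

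The consequence is confined to two components of a secondary outcome. The primary outcome, the sample size, the visit count and module completion are untouched, and crude totals can still be recovered from the planned data. This is a cheap improvement rather than a threat to the main conclusion.

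**What to change.** In Website user statistics and Secondary analyses:

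1. Add total pages viewed and total time on the site per randomised participant, in each window, as the compared engagement outcomes next to the visit count. Each total is visits × average, and zero for a participant with no visits.
2. Analyse the totals with a method suited to skewed data with zeros, such as a count-type model or a bootstrap interval.
3. Report the two per-visit averages descriptively among visitors, with the number of non-visitors per arm.
4. Where page-level logs allow, leave out questionnaire-only sessions and the coaching-only booking and set-up pages described under Video-coaching sessions, so that both intervention arms are measured on the same content.

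Cost: items 1 and 3 are wording and use data already planned. Item 2 replaces a simple linear model. Item 4 needs page- or session-level data, because visits × average cannot separate types of page. Without it, the crude totals include pages that only the coaching arm can see, and the report should say so. Comparison of per-visit averages with other studies becomes descriptive only.

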### The ‘My Activity Coach’ intervention

The ‘*My Activity Coach’* intervention will provide 4 modules with personalised physical activity feedback over an 8-week period. A new module will become available to participants every second week. In each module participants will log on to the intervention website, complete a brief survey and immediately receive computer-tailored advice based on their answers. Given that all content will be personally–tailored, there will be differences in the information that participants receive. For example, participants who are overweight or obese will receive additional information not provided to participants who are of normal weight, as this information would be irrelevant for them. Photographs of people tailored to participant’s activity levels, age and gender will be included in the feedback. The intervention will also provide participants with an action planning tool to support them in setting detailed physical activity plans during the program [39]. The content of the tailored advice and the action planning tool is described in more detail below. Every second week a new intervention module will become available to participants. The module will appear on the intervention homepage, and participants will receive an email to alert them that it is available. Participants will also receive up to two reminder emails to complete each module if they haven’t already done so. Participants who haven’t completed the module one week after it first became available will receive a reminder phone call. Participants can access and re-complete previous modules up to 12 months post-baseline.

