### Video-coaching sessions

The video-coaching sessions will take place on alternate weeks to the modules (e.g., week 1 = module 1, week 2 = video-coaching, week 3 = module 2, etc.) through an online video calling program of participants’ choice. The coaching sessions will only be available for participants in the tailoring + video-coaching group. These participants will have a ‘video-coaching’ tab on the website which will include a link to free online video calling programs including Skype, Google Hangout, Yahoo Messenger and Face Time, and information on how to set up an account. The website will also provide a link to a calendar where participants can book their time slot with the Activity Coach. They will need to book a time for each of the 4 sessions, and will be asked to do this immediately following the completion of a module (thus one week in advance of the coaching session). During the session the Activity Coach will comment on the tailored advice participants received in the module from the previous week. The Coach will ask participants if they understood the advice, if they agree with the contents of the advice (and if not, why), if they have been able to act on the advice, and if they encountered any problems adhering to the advice. The coach will also ask participants if they have any questions. The coach will ensure that the video call will be a maximum of 15 minutes in length. The sessions are purposefully designed to be short to assess whether this method can be viable for future large scale interventions, and to keep the time requirements of participants to a minimum.

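### Website-use statistics are compared between arms on site-wide counts that include coaching-only tasks, so they are not like-for-like; the label of the second usage window also needs correcting

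*Protocol article*

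**What the plan says.** **Metric.** Under Website user statistics, the protocol article lists "number of website visits, average number of pages viewed during a visit, and average visit duration during the 8 week intervention period", and the same measures "during the 12 month post intervention period leading up to the follow up questionnaires". They are collected per participant with web-analytics software, and the section does not restrict them to particular pages.

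**Comparison.** Secondary analyses states that these statistics will be compared between groups by linear mixed modelling. The Background section names website engagement as a between-group secondary outcome. Procedure limits engagement measurement to the intervention participants, so the comparison that matters is coaching against tailoring-only.

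**Coaching-only site tasks.** Under Video-coaching sessions, only the coaching arm receives a "tab on the website which will include a link to free online video calling programs", with instructions for setting up an account. The site also links to a booking calendar. "They will need to book a time for each of the 4 sessions", and each booking is requested straight after a module is finished.

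**Calendar.** The intervention provides "4 modules with personalised physical activity feedback over an 8-week period". Questionnaires fall at baseline, "immediately post-intervention at week 9, and 6 and 12 months post baseline". On access, the article says: "Participants can access and re-complete previous modules up to 12 months post-baseline".

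**The concern.** Whether brief coaching increases engagement with the web programme is one of the trial's named questions. To answer it, the measure must count the same kind of activity in both intervention arms. As written, coaching participants have site tasks (reading the tab, setting up a video account, going to the calendar) that the tailoring-only arm does not have. Those tasks enter the outcome although they say nothing about how much tailored advice was read. A difference between arms in either direction could then be taken as an effect of coaching on engagement when part or all of it comes from scheduling.

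A smaller matter is the second usage window. Its label counts 12 months from the end of the intervention, while the follow-up questionnaires and module access are counted from baseline. An analyst who applied the label literally would include weeks after the modules have closed and the last questionnaire is due.

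**Working it through.** **1. Effect of coaching tasks on the three statistics**

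The article fixes four modules, four bookings, and the request to book straight after each module. It gives no pages per visit, no visit length and no booking effort. The following are therefore assumptions:

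- a module visit has P = 8 to 15 pages and lasts D = 15 to 30 minutes;
- a booking adds b = 1 to 3 tracked pages and t = 1 to 5 minutes;
- there is one visit per module, and use of the tailored content is identical in both arms.

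Let k be the number of the four bookings made in a separate visit. Then:

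- visits = 4 + k
- pages per visit = (4P + 4b) / (4 + k)
- minutes per visit = (4D + 4t) / (4 + k)

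*All bookings in the module visit (k = 0), the path the article asks for.* Visits stay at 4. Pages per visit rise by b/P, from 1/15 = 7% to 3/8 = 38%. Duration rises by t/D, from 1/30 = 3% to 5/15 = 33%.

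*All bookings in separate visits (k = 4).* Visits go from 4 to 8. With P = 10, D = 20, b = 2, t = 2:

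- pages per visit = (40 + 8)/8 = 6, against 10 in the other arm;
- minutes per visit = (80 + 8)/8 = 11, against 20.

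*Where the direction changes.* Pages per visit fall below P once k > 4b/P, here 4 × 2/10 = 0.8. Duration falls below D once k > 4t/D, here 4 × 2/20 = 0.4. On these inputs a single separate booking already reverses both averages: 48/5 = 9.6 pages and 88/5 = 17.6 minutes.

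With no real difference in use of the content, the three statistics can therefore move apart by an amount, and for the averages in a direction, that depends on booking habits.

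**2. Second window**

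Inputs: an 8-week programme, a post-test at week 9, and the last questionnaire and end of module access at 12 months post-baseline. Twelve months = 365.25/7 = 52.2 weeks.

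| Start of window | End if 12 months follow | Past last follow-up | Weeks available to 12 months post-baseline |
|---|---|---|---|
| Week 8 | 8 + 52.2 = week 60.2 (13.8 months) | 8 weeks (8/52.2 = 15%) | 52.2 − 8 = 44.2 |
| Week 9 | 9 + 52.2 = week 61.2 (14.1 months) | 9 weeks (9/52.2 = 17%) | 52.2 − 9 = 43.2 |

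The stated 12 months after the intervention cannot be reproduced from the trial's own calendar, which leaves roughly 10 months.

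**The case against.** A reader might infer that the coaching arm is bound to look more engaged. The article does not support that, for these reasons:

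- The site gives a link to a calendar, which may lie outside the tracked site. Only the tab and its set-up information are clearly on it, and set-up is presumably done once.
- Booking is requested straight after a module. If done then, it adds no visit, so a doubled visit count is not the intended path.
- Two of the three statistics are per-visit averages, which separate short visits can lower.
- Tailoring-only participants receive four tailored emails, meant to balance the number of contacts. These may bring them back to the site.

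These points remove any claim of a known upward bias. They do not make the measure comparable: the emails balance contacts, but they do not take coaching-only pages out of the counts.

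It is also fair to say that website statistics are only part of engagement. Measures pairs them with intervention fidelity, which includes completion and timing of the module surveys. Both arms share those, and the coaching tab does not enter them. This limits the damage, but the website statistics are still to be compared in their own right.

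Page filters could be left to an analysis plan that is not shown. However, the article itself defines the statistics at site level and commits to comparing them, so the definition needs a restriction wherever it is finally written.

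On the window, a reader might infer that the trial has no such period at all. That goes too far. The wording ties the period to the follow-up questionnaires, so the intended end is recoverable, and the mislabelling applies equally to both arms.

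**Conclusion.** The concern stands as a comparability problem in one component of a secondary outcome. Site-wide visits, pages per visit and visit duration mix coaching logistics with use of the tailored content in one arm only, so a between-arm difference cannot be read as a difference in engagement with that content. Neither size nor net direction can be computed from the article. The 7% to 38% and 3% to 33% ranges, and the fall from 10 to 6 pages and from 20 to 11 minutes, rest wholly on the assumed page counts and times and on bookings being tracked. They show only that the distortion could matter and could go either way. The primary outcome is not affected.

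The window is a minor correction. Read literally it overruns the last questionnaire and module access by 8 to 9 weeks. It is a mislabelled period of about 44 weeks (43 if counted from week 9) and creates no bias between arms.

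**What to change.** 1. For the between-arm comparison, define the website statistics on content common to both intervention arms (module, tailored-advice and action-plan pages). Exclude the video-coaching tab and any booking pages. State how a visit consisting only of excluded pages is handled; the natural rule is not to count it.
2. Report total site use descriptively by arm.
3. Reword the second window to run from the end of the intervention to 12 months post-baseline, about 44 weeks, so that it agrees with the questionnaire schedule and the access period.

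The cost is two edited sentences and a page filter in the usage export. The small downside is that usage must be reported by page rather than for the whole site. This is best settled before data collection, because per-visit averages exported for the whole site cannot be split by page afterwards.
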